**Methods/design:**

The study will enroll at least 510 US women aged 25–64 years who report no Pap test in the last 4 years and no HPV test in the last 6 years. We will randomize participants to an intervention or control arm. The intervention arm will receive kits to self-collect a sample at home and mail it for HPV testing. In both the intervention and control arms, participants will receive assistance in scheduling an appointment for screening in clinic. Study staff will deliver HPV self-collection results by phone and assist in scheduling participants for screening in clinic. The primary outcome is completion of cervical cancer screening. Specifically, completion of screening will be defined as screening in clinic or receipt of negative HPV self-collection results. Women with HPV-negative self-collection results will be considered screening-complete. All other participants will be considered screening-complete if they obtain co-testing or Pap test screening at a study-affiliated institution or other clinic. We will assess whether the self-collection intervention influences participants’ perceived risk of cervical cancer and whether perceived risk mediates the relationship between HPV self-collection results and subsequent screening in clinic. We also will estimate the incremental cost per woman screened of offering at-home HPV self-collection kits with scheduling assistance as compared to offering scheduling assistance alone.

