### Intervention and control procedures

Women assigned to the intervention arm will receive an HPV self-collection kit by mail, which will include an informational sheet, instructions, and materials to self-collect a cervico-vaginal sample, and a pre-paid envelope to return it by mail (Fig. 1). When HPV self-collection test results are available, ASHA staff will call the participant to deliver her HPV results and schedule her for a free appointment in clinic regardless of the result. Women who with self-collection HPV-positive results will be informed that their results indicate a higher risk for cervical cancer and will be advised to schedule an appointment to complete Pap/HPV co-testing at a study clinic (see results delivery scripts, Additional file 1: Appendix 1). Women with self-collection HPV-negative results will be told that their results indicate lower risk for cervical cancer, but that doctors cannot use self-collection results to make decisions about their care. Participants with both HPV-negative and HPV-positive self-collection results will be able to schedule an appointment for free screening in clinic during the HPV results delivery call. Participants whose self-collection results are inconclusive will be contacted and given the option to try the self-collection again or schedule a clinic appointment. A participant who has not returned a self-collected sample within 3 weeks will receive a mailed reminder letter to return the kit. If the kit still has not been returned 2 weeks later, she will receive a reminder call, at which point she will receive assistance to schedule a clinic appointment if she prefers.

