#### Secondary outcomes and other measures

Secondary trial outcomes include perceived likelihood of cervical cancer, worry about getting cervical cancer, and embodiment of risk (Fig. 2). These constructs come from the health belief model (HBM) [33], which posits that an increase in the perceived risk of cancer will be associated with increased intention and subsequent completion of cancer screening [32, 56]. Perceived risk has a cognitive aspect, operationalized as *perceived likelihood* of developing cervical cancer, and an affective aspect, operationalized as *worry*. For the present trial, we added an exploratory risk construct, *embodiment of risk,* which is similar to experiential risk in the TRIRISK model, which we operationalize as awareness of and a sense of connection with one’s body as a source of health and risk [57, 58].

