To examine possible mechanisms explaining the intervention effect, a standard mediation analysis will be performed by (1) establishing whether the exposure of interest (receipt of HPV-positive result via self-collection) is associated with the outcome (screening in clinic) and mediating variables (e.g., perceived risk), and then (2) determining whether controlling for the mediators meaningfully reduces the size of the association between the exposure of interest and outcome. We will compare completion of screening in clinic in women in the intervention arm who return a self-collected sample and receive a positive HPV self-collection result and in (i) women in the intervention arm who do *not return* a self-collection sample (“non-returners”) and (ii) all women in the control arm, using exact logistic regression (adjusting for baseline covariates and potential confounders). HBM constructs will be evaluated as potential mediators of any observed association. The MacKinnon method will be used to compare coefficients for the intervention-behavior pathway, before and after controlling for the mediator, using the Sobel test [59, 60]. Appropriate methods for handling missing data (e.g., baseline value carried forward or multiple imputation) will be employed to account for unobserved mediator variables. If the intervention is not found to be effective, we will still conduct the mediation analysis to examine suppression (i.e., if the intervention increases one belief but reduces another, these changes could offset one another in how they affect behavior).

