#### Power calculations

A total of 510 participants in a 2:1 randomization ratio of intervention to control provides 88–94% power to detect a 15% or greater difference between arms for the primary outcome, assuming intervention-arm screening completion of 60–80%, which would be consistent with previous studies [47, 65]. A rate of 13% HPV messenger RNA (Mrna) positivity (as detected in MBMT2 using the Aptima HPV assay in the same target population [47]) and a 70% return of kits in the intervention arm will provide 80–85% power to detect a 30% difference in uptake of clinic screening between participants with self-collection HPV-positive results and other subgroups for mediation analysis.

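### The mediation analysis is presented as explaining the intervention's effect, but its exposure is an HPV-positive result, which cannot identify the effect of the randomized offer on perceived risk

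*Protocol article*

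**What the plan says.** The protocol article states its interest in perceived risk in several places.

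- **Abstract, Methods/design:** "We will assess whether the self-collection intervention influences participants’ perceived risk of cervical cancer". The same sentence then asks a second question: whether perceived risk mediates between HPV self-collection results and later clinic screening.
- **Objectives:** the hypothesis is that offering self-collection raises screening completion through an increase in perceived risk.
- **Secondary outcomes and other measures:** "Secondary trial outcomes include perceived likelihood of cervical cancer, worry about getting cervical cancer, and embodiment of risk".
- **Analytic approach and power, mediation paragraph:** this is the only stated analysis of these beliefs. It is offered as an account of the intervention's effect, and its first step is "establishing whether the exposure of interest (receipt of HPV-positive result via self-collection) is associated with the outcome (screening in clinic) and mediating variables". Women with a positive result are compared with (i) intervention-arm women who returned no sample and (ii) all controls. The paragraph then refers to a pathway from intervention to behavior. It ends with a check for suppression should the intervention prove ineffective: "if the intervention increases one belief but reduces another, these changes could offset one another in how they affect behavior".
- **Intervention and control procedures:** "Women with self-collection HPV-negative results will be told that their results indicate lower risk for cervical cancer". Women with a positive result are told the opposite.

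**The concern.** Two different exposures are in play. One is the randomized offer of a kit, which the first question in the abstract, the hypothesis and the suppression check all concern. The other is receipt of a positive result, which depends on two events after randomization: returning a kit and testing positive. The mediation paragraph fixes the second exposure and describes the analysis in the language of the first.

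If it is followed as written, the hypothesis in Objectives and the suppression question would be answered from a non-randomized comparison that leaves out most of the intervention arm. A rise in perceived risk among women told they are HPV-positive could then be read as the way the offer works, although the offer may have changed average perceived risk little, or in the other direction.

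**Working it through.** **Inputs (Power calculations).** 510 women allocated 2:1, so 340 to the intervention and 170 to control; intervention-arm completion of 60–80%; kit return of 70%; and "A rate of 13% HPV messenger RNA (Mrna) positivity". Alpha is not stated there; two-sided 0.05 is assumed.

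**The plan's own figures.** For 340 v 170 and a 15-point difference, power is 89.5% (60% v 45%) to 95.1% (80% v 65%), within 2 points of the stated 88–94% at each end. For 31 v 102 and a 30-point difference in clinic uptake, exact (Fisher) power is 82–85% for comparator uptake of 30–50%, in line with the stated 80–85%. For 31 v 170 it is 87–89% over the same range. So about 31 exposed women is the plan's own design figure, and no stated figure is in error.

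**Who is in the contrasts.**

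| Group | Calculation | Women | Share of arm | In the contrasts? |
|---|---|---|---|---|
| HPV-positive | 340 × 0.70 × 0.13 | 30.9 | 9.1% | exposed |
| HPV-negative | 340 × 0.70 × 0.87 | 207.1 | 60.9% | no |
| Non-returners | 340 × 0.30 | 102 | 30% | comparator (i) |
| Controls | 510 / 3 | 170 | – | comparator (ii) |

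**What the arm effect is made of.** Let a positive result raise a perceived-risk score by a SD, a negative result lower it by b SD, and non-return leave it unchanged, each relative to control. Ignoring inconclusive and undelivered results,

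arm effect = 0.091a − 0.609b.

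The HPV-positive contrast estimates a, if selection into the exposed group is set aside. The documents give neither a nor b, so the following values are assumptions:

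| a | b | HPV-positive contrast | Arm effect |
|---|---|---|---|
| 0.5 | 0 | +0.5 | 0.0455 |
| 0.5 | 0.05 | +0.5 | 0.0455 − 0.0305 = +0.015 |
| 0.5 | 0.10 | +0.5 | 0.0455 − 0.0609 = −0.015 |
| 0.5 | 0.20 | +0.5 | 0.0455 − 0.1218 = −0.076 |

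The sign changes at b/a = 0.091 / 0.609 = 0.149. Even with b = 0, the arm effect is only 9.1% of the HPV-positive contrast.

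**Precision, complete data, SD units.** SE = √(1/n₁ + 1/n₂); the difference detectable at 80% power is 2.80 × SE.

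- 31 v 102: SE 0.205, detectable 0.57
- 31 v 170: SE 0.195, detectable 0.55
- 340 v 170: SE 0.094, detectable 0.26

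These belong to different estimands. They show what each contrast can resolve, not that one can stand in for the other.

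**The case against.** The strongest reply is that the HPV-positive analysis is deliberate and answers a question the protocol does ask. The second half of the abstract's sentence poses mediation between HPV results and clinic screening, with the same exposure and outcome as the mediation paragraph. The Randomization section gives responses of HPV-positive women as the reason for 2:1 allocation, and Power calculations sizes that contrast. All of this stands, and the contrasts should stay.

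It can also be said that a missing between-arm model for the beliefs is a detail for a separate analysis plan. The design would support one: Table 1 collects the beliefs at baseline and after the intervention, and interviewers are blinded to arm for those items. This stands too. A reader might infer that the trial will make no arm comparison of perceived risk, but silence in an article does not show that. What does not fall away is that the article itself assigns an HPV-positive exposure to an analysis it describes as explaining the intervention.

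On suppression, two beliefs moving in opposite directions can be estimated within the HPV-positive contrast, so it would be wrong to say the check can detect nothing. It would, however, detect offsetting responses to a positive result, whereas the clause is about the offer.

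Lastly, the smaller standard error of the arm contrast does not make it more powerful in every case. In the −0.076 SD example its power is about 13%, against about 73% for 0.5 SD in HPV-positive women v controls. The argument for the arm comparison is that it answers the question posed, not that it is more likely to be significant.

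**Conclusion.** The point holds as a mismatch between question and exposure. The HPV-positive contrasts suit the question about response to a result. They cannot identify the effect of the randomized offer on perceived risk, because about 61% of the arm is in neither contrast and the exposed group is formed after randomization; covariate adjustment does not restore the randomized comparison.

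The group sizes follow directly from the plan's inputs. The possible dilution or reversal rests on assumed values of a and b and on no change in non-returners. A reader might infer that the arm effect is negative, or that the HPV-positive contrast says nothing about the intervention. The documents support neither: they give no effect sizes for beliefs, and response to a positive result is one component of the arm effect.

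The primary analysis of screening completion is unaffected. The change should be made, because the stated mechanism and the secondary outcomes could otherwise be misread.

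**What to change.** In the mediation part of Analytic approach and power:

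1. Analyse each perceived-risk outcome by randomized arm in all randomized women: post-intervention score on arm, adjusted for the baseline score listed in Table 1.
2. Base the hypothesis in Objectives and the suppression check on arm as the exposure. State which outcome is meant, since clinic screening differs from the primary outcome, which also counts a negative self-collection result as complete.
3. Keep both HPV-positive contrasts, labelled as non-randomized analyses of response to a positive result. For these, replace the references to the intervention effect and the intervention-behavior pathway with wording that names the positive result as the exposure.

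The missing-data options can stay as they are. The cost is some rewording and one further regression per outcome, on data already scheduled in both arms. The downside is that the arm effect on perceived risk may prove smaller, or less favourable to the hypothesis, than the HPV-positive contrast.

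### No planned mediation contrast varies the HPV result among women who returned a kit, and the contrasts named are confounded by kit return: plainly against non-returners, less against controls

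*Protocol article*

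**What the plan says.** Under Analytic approach and power, the protocol article sets out a mediation analysis whose exposure is receipt of an HPV-positive result by self-collection and whose outcome is screening in clinic. The index group is intervention-arm women "who return a self-collected sample and receive a positive HPV self-collection result and in (i) women in the intervention arm who do" not return a sample. The second comparator is "all women in the control arm, using exact logistic regression", with adjustment for baseline covariates and potential confounders. Women who returned a kit and tested HPV-negative are in neither comparator, and no reason is given.

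The abstract gives the aim as assessing "whether perceived risk mediates the relationship between HPV self-collection results and subsequent screening in clinic". Objectives and the opening of the mediation paragraph state a wider purpose: to explain why the intervention works or does not.

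Under Intervention and control procedures, staff call each returner with her result and "schedule her for a free appointment in clinic regardless of the result". Clinic attendance is therefore a possible outcome for HPV-negative women too. Power calculations assumes "A rate of 13% HPV messenger RNA (Mrna) positivity" and "a 70% return of kits in the intervention arm will provide 80–85% power to detect a 30% difference in uptake of clinic screening" between HPV-positive women and subgroups that it does not name.

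**The concern.** Three features of the named contrasts cause difficulty.

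- **Selection on kit return.** Every HPV-positive woman chose to return a kit, and no woman in the first comparator did. Women who complete one step may be more likely to complete the next, whatever their result. The control arm contains would-be returners and would-be non-returners together, so the same bias is present but diluted.
- **Non-return can reflect the outcome.** A woman who has not returned her kit gets a letter at 3 weeks and a call 2 weeks later, when she can be helped to book a clinic visit if she prefers that. Some non-returners may be women who chose the clinic. This bias runs the other way.
- **Different clocks.** Controls are called 1 week after enrollment, non-returners at about 5 weeks (3 + 2), and returners when results are available. If clinic screening is counted over a fixed time from enrollment, controls have longer to attend after contact.

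HPV-negative returners passed the same selection step, receive a results call, can book the same free visit, and are surveyed 1 week after result delivery. They are the only other group defined by a result. Without them, an association between a positive result, perceived risk and attendance cannot be separated from readiness to engage. The 2:1 allocation was chosen to support analyses of HPV-positive women, and the Discussion lists the psychological mediators as a major strength, so the point matters to the trial's own claims.

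**Working it through.** **Inputs from the document (Power calculations).** "A total of 510 participants in a 2:1 randomization ratio of intervention to control provides 88–94% power"; 70% kit return; 13% positivity; a 30-point detectable difference; stated power 80–85%.

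**Assumed.** Two-sided 5% level, and comparator clinic uptake of 30–50%. The document gives neither for this calculation.

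**Expected groups.** Intervention arm 510 × 2/3 = 340; control arm 170.

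- HPV-positive returners: 340 × 0.70 × 0.13 = 30.9, about 31
- HPV-negative returners: 340 × 0.70 × 0.87 = 207
- Non-returners: 340 × 0.30 = 102

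**Plan's own figure.** Power of Fisher's exact test for a 30-point difference, by enumeration, with 31 HPV-positive women:

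| Comparator | n | Power |
|---|---|---|
| Non-returners | 102 | 82–85% |
| All controls | 170 | 87–89% |
| HPV-negative returners (not planned) | 207 | 86–89% |

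The stated 80–85% fits the non-returner comparison. Sample size gives no reason to leave out the HPV-negative returners.

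**Size of the selection effect when the result does nothing.** Let r be clinic attendance in returners and q in non-returners. The false difference is then r − q against non-returners. Controls are a mixture attending at 0.70r + 0.30q, so the false difference against them is r − (0.70r + 0.30q) = 0.30(r − q). In this model the control comparison carries 30% of the bias.

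*Model 1 (assumed).* A latent engagement trait raises the log-odds of return (70% overall) and of attendance (45% overall) with the same slope per standard deviation:

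| Slope | Against non-returners | Against controls |
|---|---|---|
| 0.5 | +5.5 points | +1.7 points |
| 1.0 | +17.2 points | +5.2 points |

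*Model 2 (assumed rates).* The last two columns give how often a pooled two-proportion test would declare a difference:

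| r | q | Against non-returners | Against controls | Declared, non-returners | Declared, controls |
|---|---|---|---|---|---|
| 60% | 30% | 30 points | 9 points | 86% | 15% |
| 50% | 30% | 20 points | 6 points | 53% | 9% |
| 40% | 30% | 10 points | 3 points | 19% | 5% |

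In the first row, selection alone produces the full planned detectable difference against non-returners.

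In both models the difference against HPV-negative returners is zero, but only because a negative result is given no effect. These figures are unadjusted and include neither the clinic-preference effect nor the contact-timing effect. They show how large one source of bias could be; they are not net estimates.

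**The case against.** Much of the case on the other side stands.

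- **The control comparison suits part of the aim.** Explaining the intervention effect calls for a reference without a kit or result, and the randomized control arm supplies it. Its selection bias is modest in the models above. That is a reason to keep it.
- **Adjustment is planned.** Table 1 collects baseline knowledge, barriers, self-efficacy and worry, which are plausible proxies for engagement. Adjustment may reduce the bias. It cannot be relied on to remove it, and about 31 exposed women support few covariates.
- **Biases oppose each other.** Clinic preference among non-returners and the earlier call to controls would tend to raise comparator attendance. The net direction is therefore uncertain.
- **HPV-negative returners are not a neutral reference.** They are told that their result indicates lower risk, and they already count as screening-complete. If that reassurance cut attendance from an assumed 45% to 25%, the contrast would show 20 points with no effect of a positive result. HPV status is also not randomized among returners.

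A reader might infer that the planned analysis measures only willingness to return a kit, that the whole mediation aim is uninterpretable, or that HPV-negative women should replace the named comparators. The document supports none of these. The contrasts mix willingness with the effect of the result, the control contrast is only mildly affected, and replacement would change the question being answered.

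**Conclusion.** The concern holds as a gap and a matter of interpretation in a secondary mechanism analysis. The comparison with non-returners is confounded by self-selected kit return, and the comparison with controls is confounded to a smaller degree. No planned contrast varies the result among women who returned a kit, although the abstract's aim concerns self-collection results.

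Under Model 1, with no effect of the result, the false difference is 5.5 to 17 points against non-returners and 1.7 to 5 against controls. This rests on the assumed slopes of 0.5–1.0, the assumed 45% attendance, no adjustment and no opposing bias. The group sizes follow from the protocol's own 70% and 13%. No stated number is wrong: the mediation power is reproduced, and the primary intent-to-treat comparison does not depend on these contrasts.

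**What to change.** Under Analytic approach and power, in the mediation paragraph:

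1. Add HPV-negative kit returners as a third comparator for receipt of an HPV-positive result. Count clinic screening over the same window after result delivery in both groups, and adjust for age and baseline beliefs.
2. Keep the control comparison for the question of how the intervention works.
3. State what each contrast estimates, and say that the non-returner comparison, and to a lesser degree the control comparison, is confounded by kit return.

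The cost is wording only. Clinic attendance and the survey after result delivery are already collected for these women, and power for the added contrast is adequate. There is a small downside: the added contrast estimates positive versus negative result, including any reassurance from a negative one, and not positive result versus no result. The text should say so.

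### The mediation analysis compares logistic coefficients before and after adjustment with a Sobel test in about 31 exposed women, which understates mediation, and the quoted 80–85% power does not apply to it

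*Protocol article*

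**What the plan says.** In the protocol article, under Analytic approach and power, the mediation exposure is receipt of an HPV-positive self-collection result and the outcome is screening in clinic. The HPV-positive women are compared with intervention-arm women who did not return a kit, and separately with all controls, "using exact logistic regression (adjusting for baseline covariates and potential confounders"). Mediation is judged by whether the exposure-outcome association shrinks to a meaningful degree once the mediators are in the model. The MacKinnon method is used "to compare coefficients for the intervention-behavior pathway, before and after controlling for the mediator, using the Sobel test". Two examples are given for missing mediators: "baseline value carried forward or multiple imputation". If the intervention proves ineffective, the analysis will still be run to look for suppression, meaning that gains in one belief are offset by losses in another.

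Under Power calculations, the article gives "80–85% power to detect a 30% difference in uptake of clinic screening between participants with self-collection HPV-positive results and other subgroups", and says this is for the mediation analysis. No power is given for an indirect effect.

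**The concern.** Three features of the method act against finding mediation, and one label invites misreading.

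- **Coefficient comparison.** Odds ratios are not collapsible. Adding a variable that predicts the outcome raises the exposure coefficient even if the exposure does not affect that variable. Mediation lowers the coefficient, so the two movements partly cancel.
- **Sobel test.** It treats the product of two estimates as normal. With small paths and few exposed women the product is not normal, and the test is conservative.
- **Baseline carried forward.** A woman with no post-intervention survey is assigned a belief change of exactly zero, whatever her result did to her perceived risk.
- **Power statement.** A reader may take 80–85% as the chance of detecting mediation.

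The trial's hypothesis (Objectives) is that screening rises because perceived risk rises. The Discussion lists mediation as a major strength, and the 2:1 allocation is justified by analyses of HPV-positive women. A null mediation result from this method could be read as evidence against the mechanism when the method was unlikely to detect it.

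**Working it through.** **Inputs from Power calculations.** "A total of 510 participants in a 2:1 randomization ratio of intervention to control"; "A rate of 13% HPV messenger RNA (Mrna) positivity"; "a 70% return of kits in the intervention arm".

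- Intervention arm: 510 × 2/3 = 340. Controls: 170.
- Returners: 340 × 0.70 = 238. Non-returners: 102.
- HPV-positive (exposed): 238 × 0.13 = 30.9, about 31.

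**The plan's own power figure.** Two-sided alpha of 0.05 is assumed, since none is stated. Exact enumeration of Fisher's test for a 30-point difference gives:

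| Reference uptake | 31 v 102 | 31 v 170 |
|---|---|---|
| 30% | 82.6% | 87.2% |
| 40% | 82.8% | 86.8% |
| 50% | 84.6% | 89.2% |

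The stated 80–85% is therefore reproduced as a two-proportion comparison of HPV-positive women with non-returners. That is the total association and contains no mediator.

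**Coefficient shift with no mediation.** Take a standardized mediator with the same distribution in both groups (exposure-to-mediator path a = 0) and mediator effect b on the log-odds. For uptake of 40% v 70% the unadjusted coefficient is ln(0.7/0.3) − ln(0.4/0.6) = 0.847 + 0.405 = 1.25. The adjusted coefficient that yields the same two proportions, by numerical integration over the mediator, is:

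| b per SD | Adjusted | Unadjusted minus adjusted | As share of unadjusted |
|---|---|---|---|
| 0.4 | 1.30 | -0.05 | -4% |
| 0.7 | 1.39 | -0.13 | -11% |
| 1.0 | 1.51 | -0.25 | -20% |

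The shift scales with the total coefficient. With somewhat smaller totals, large simulated samples give about -0.04, -0.12 and -0.21.

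With real mediation, large samples show the shortfall. For a = 0.5 and b = 0.5 the before/after drop is 0.169 against a product a × b of 0.25 (68%). For a = 0.5 and b = 1 it is 0.206 against 0.498 (41%).

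Rescaling the coefficients to a common latent variance removes most of the shift: for a = 0 and b = 0.5, 1.0 and 1.5 it falls from -0.07, -0.25 and -0.51 to -0.02, -0.06 and -0.09.

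**Sobel test.** The simulation uses a linear model for the mediator, a Wald logistic model for the outcome, 40% v 70% uptake, no covariates and no missing data. The path sizes are assumptions; the article gives none. Results move by one or two points between runs.

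| a (SD) | b (log-odds per SD) | Sobel, 31 v 102 / 31 v 170 | Joint significance, 31 v 102 / 31 v 170 |
|---|---|---|---|
| 0.5 | 0.4 | 17% / 28% | 40% / 54% |
| 0.5 | 0.7 | 44% / 60% | 65% / 73% |
| 0.8 | 0.4 | 39% / 61% | 54% / 76% |
| 0.8 | 0.7 | 83% / 94% | 93% / 98% |

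By share of the 30-point difference mediated, with equal paths assumed, Sobel power is 5% / 11% at a 10% share, 28% / 47% at 20%, 59% / 77% at 30% and 93% / 98% at 50%. Type I error is 0.0–0.1% when both paths are zero and roughly 1–4% when only a is zero, against a nominal 5%.

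**Baseline carried forward.** If a fraction m of surveys is missing equally in both groups, the groups have equal beliefs at baseline and the comparison group's beliefs do not change, the estimated path is (1 − m) × a. For a = 0.5 SD, an assumed m of 10–30% gives 0.45 to 0.35 SD. The missing rate is not given in the article.

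**The case against.** Several replies have force.

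- **Power is not low across the board.** This stands. If about half the effect is mediated, or both paths are at the upper end of the grid, the Sobel test has ample power. The loss is for small to moderate indirect effects, and the path sizes are assumed.
- **The coefficient scale is unknown.** The MacKinnon method is defined in cited sources that are not shown. If those coefficients are rescaled, most of the drift goes. The article does not say, so the point is conditional on the raw scale.
- **The power sentence is accurate.** It names a "difference in uptake of clinic screening between participants with self-collection HPV-positive results and other subgroups for mediation analysis", and the figure reproduces. Only the closing reference to mediation invites misreading.
- **Carrying baseline forward is only an example, and missing-data detail belongs in an analysis plan.** Partly fair. But the article names it as appropriate for a hypothesis about change in belief, which is a poor choice to put on record.

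Two stronger readings are tempting and are not supported. A reader might infer that the Sobel test will manufacture suppression. With a = 0 it gave a significant negative result in at most about 2% of simulated trials, and the article defines suppression as opposing effects on different beliefs, not as a rise in one adjusted coefficient. A reader might also infer that exact logistic regression would collapse to a nearly degenerate distribution here. That depends on the number and scaling of covariates, which the article does not give, and no calculation shows it.

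**Conclusion.** The concern holds in a limited form. On the raw logistic scale, the before/after comparison is biased against finding mediation, by about -0.04 to -0.21 on the log-odds scale for mediator effects of 0.4 to 1.0 per SD. With about 31 exposed women the Sobel test gives up some 4 to 26 points of power relative to joint significance over the assumed grid (98 − 94 = 4 at the strongest corner, 54 − 28 = 26 at the weakest). Baseline carried forward, if used, weakens the exposure-to-mediator path further. The 80–85% figure is correct for the quantity it names but says nothing about the indirect effect.

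This rests on the assumed path sizes, two-sided alpha of 0.05, no covariates, and Wald models standing in for exact regression. It concerns a mechanistic analysis and leaves the intent-to-treat comparison of screening completion untouched. It is worth changing because mediation is part of the stated hypothesis and the remedy is cheap.

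**What to change.** 1. Replace the coefficient comparison and Sobel test with natural direct and indirect effects on the probability scale, from regression-based causal mediation, with bootstrap intervals. If the coefficient comparison is kept as a supplement, state that the coefficients are rescaled.
2. Delete baseline value carried forward. Keep multiple imputation, with HPV result, baseline belief and the screening outcome in the imputation model.
3. In Power calculations, state that 80–85% refers to the total difference in clinic uptake between HPV-positive women and the comparison groups, not to the mediated effect.

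The cost is rewording, a little more analysis work with standard software, and a less favourable-looking power statement. No extra data are needed. The bootstrap approach was not simulated here for 31 exposed women, so its interval coverage should be checked by simulation before the analysis is fixed. Like the current method, it assumes no unmeasured confounding of exposure, mediator and outcome.
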